## Abstract

**Background:**

Since 2009 some German health insurance companies have implemented integrated mental health care services along the principles of assertive community treatment in collaboration with local mental health service providers across Germany. Focus of this study is the analysis of effectiveness and cost-effectiveness of this integrated care programme compared to care as usual in routine care surroundings in five regions in Germany.

**Methods:**

In this 18-month multi-centre observational trial 250 patients enrolled in an integrated mental health care programme and 250 patients who receive treatment as usual from five catchment areas will be included. In addition, in each group about 125 relatives of the participating patients will be included. The primary outcome criterion is the improvement of empowerment; secondary outcomes are subjective quality of life, functional impairment and costs of illness. Data will be collected at baseline and three follow-ups after 6, 12 and 18 months. Data will be analysed by means of mixed effects regression models. Propensity score methods are used for selection bias control.

**Discussion:**

Study results are expected to provide information about how integrated care programmes in their present form contribute to the improvement of mental health care. In addition, the study will provide hints to weaknesses of the current integrated care programme and options to overcome them. The major strengths of this study are the real-world character of the study intervention with a simultaneous high level of academic rigour. However, the fact that patients are not randomised to study groups and that there is no blinding might limit the study.

**Trial registration:**

German Clinical Trial Register DRKS00005111.

## Background

Contemporary treatment of people with permanent severe mental illness is not only aimed at the control of symptoms of disease but also aims at the empowerment of patients by increasing their capacities for a largely independent lifestyle and comprehensive social and professional inclusion. For this purpose adequate mental health care requires a broad spectrum of medical and psychosocial services. In order to keep the level of psychiatric inpatient treatment and institutional care as low as possible these services should be provided by multi-professional community mental health teams organized according to the principles of Assertive Community Treatment (ACT).

The concept of ACT has already been developed and tested in the 1970s in the USA. In line with the ACT model, Stein and Santos [1] developed a concept for a comprehensive multi-professional psychiatric treatment programme in the immediate residential environment of the patient which still serves as a model for community mental health interventions across the world. Subsequently, several modifications of the ACT concept, as intensive case management (ICM), community mental health teams (CMHT), and home treatment (HT) were developed to account for specific requirements and conditions of the respective structures of psychiatric care.

In a systematic review on the effectiveness and efficiency of these treatment approaches for the period between 1979 and 2003, Roberts et al. evaluated a total of 48 publications written in English, of which 18 were from the United States and 15 from the United Kingdom. Twelve of the studies examine the cost-effectiveness of ACT in comparison to the respective psychiatric standard care during the period 1972 to 1996, the others focus on case management, community psychiatric nurses and other forms of community psychiatric care [2]. The authors conclude on the basis of the included studies – as already done in a previous review [3] - that the investigated ACT programmes, with few exceptions, prove to be more efficient compared to inpatient treatment [2]. Rosen et al. [4] and Knapp et al. [5] came to a similar conclusion. For case management and intensive case management programmes, the authors concluded that case management compared with standard inpatient treatment is cheaper and more effective, but there are no differences compared to standard outpatient treatment [2]. Roberts et al. claim that data are inconclusive for the other treatments which were investigated within their review [2].

A Cochrane review by Marshall and Lockwood [6] of ACT for people with severe mental disorders demonstrated benefits of ACT compared to standard care with respect to hospital admissions, length of hospital stay and, as a consequence, reduced costs of hospital care. Even if total costs are not lowered by ACT, patients benefit from the intervention due to better accommodation status, more employment and higher satisfaction scores. Furthermore a lower loss-to-follow up-rate is reported. Mental state and social functioning are not affected. ACT is more effective even compared to case management as regards duration of hospitalisation and costs of hospital care [6].

These results are largely in agreement with the results of another Cochrane review of intensive case management [7]. This review planned to replace the previous one written by Marshall and Lockwood. However, as the new review focuses on intensive case management (ICM), which, in this case, is defined as ACT and CM in combination with a caseload less than 20 [7], the older review remains crucial concerning ACT itself. In general, the updated review reported fewer effects than the former one. For example, there is no longer a benefit as regards employment status, and data for cost reduction are inconclusive. Burns et al. [8] assume that the inconsistent effects over recent years might be explained by differences in trial contexts. In the meantime, welfare systems have developed a number of interventions with a view to reducing hospitalisation. Thus, control groups might be contaminated with other care services and consequently, effect sizes could be reduced. Burns et al. showed, in a systemic review including 29 trials, that the more ICM is adherent to the ACT model, the lower is duration of hospitalisation. Moreover, benefits regarding use of hospital care are more pronounced in patients with a high baseline level of hospitalisation. As new welfare systems generally aim at lower reliance on hospitals, use of hospital care at baseline is reduced in newer studies and consequently, significant reduction in costs for hospital care and also in total costs is more difficult to obtain. Thus, clinical benefits become more and more important to justify the implementation of ACT services [3].

In summary, there is very good evidence for the effectiveness of ACT compared to inpatient treatment and standard care, because it achieves better results in terms of reducing social impairments at comparable costs. However, effectiveness and cost-effectiveness of each community mental health care programme has to be evaluated in its special setting both in terms of real implementation and in terms of patients’ characteristics. Attention must be paid to unchanged costs not outweighing clinical and social benefits as in the end cost-effectiveness is what really counts.

### The situation of mental health care services in Germany

Germany is one of the countries with highest expenditure for mental health care in the world. However, in contrast to other western European countries, psychiatric treatment in Germany is still mainly provided by psychiatric hospitals, outpatient clinics and office based psychiatrists and only rarely by community mental health teams. As mental health policy, except the provision of pharmaceutical treatment, is the responsibility of the federal states, no national mental health plan exists. Therefore, community mental health care systems vary widely with regard to conceptual, organisational and economic conditions across the country. Moreover, the fact that different components of community mental health care are funded by different payers (and on different legal bases) hampers coordination and integration of services.

Meanwhile an increasing number of experts suspect that the lack of national standards for community mental health care provision leads to deficits in service effectiveness and efficiency. As the only possibility to directly influence the design of community mental health care, the federal government, in recent years, has introduced several changes to the Social Security Code which forms the legal basis for health care financing. These legal changes allowed health insurance companies to enter into contracts with medical or non-medical mental health service providers for the financing of complex medical and psychosocial services for people with mental disorders which is a basic requirement for the provision of assertive community treatment. As a result of these legislative changes, some of the 146 German health insurance companies started to implement integrated mental health care services along the principles of ACT in collaboration with local mental health service providers. To date, there are only few systematic trials on the effectiveness and cost-effectiveness of these integrated services. Only regional pilot projects have been evaluated and most of these studies are limited by methodological shortcomings.

Within the framework of an analysis of a programme for integrated care (IC) of patients with schizophrenia developed on the basis of the ACT approach Karow et al. concluded that patients who were treated in the ACT programme showed a greater improvement in psychosocial and clinical outcome parameters after 12 months than patients in routine care. This study also showed a reduction in expenses for inpatient treatment with a simultaneous increase in expenses for outpatient treatment and no significant differences in total costs between both programmes were revealed. However, as part of a cost-effectiveness analysis, the authors demonstrated that treatment efficiency (relationship between treatment costs and gain in quality of life) in the ACT group was better than in routine care [9,10].

As result of a mirror design study Fischer et al. concluded that IC reduces inpatient hospitalisation by offering a complex range of services in the outpatient setting. However, there is only a shift from inpatient treatment to outpatient care and total expenditures did not change significantly [11].

Hence, studies conducted in Germany confirm the results of international studies: intensified outpatient services do not contribute to a reduction of psychiatric treatment costs but to increased efficiency of psychiatric treatment. The results of the research Karow et al. [9] suggest that, in these cases, similar effects were achieved irrespective of programme design. However, since only pilot projects have been investigated so far, a verification of these effects and the identification of influencing factors under real life conditions of care are pending.

Also, research needs to address the issue of whether integrated care programmes affect relatives or informal carers living with patients with severe mental disorders. It is assumed that family members and informal carers perceive greater personal involvement in integrated care programmes as positive. On the other hand, there is a possibility that the shift of treatment from the inpatient to the outpatient sector is associated with additional burden for relatives and informal carers.

While most of the earlier contracts on integrated psychiatric care were limited to particular regions, one of the larger health insurance companies started in 2009 to enter into identical contracts named “Network for mental health” (NWpG) with different service providers in different regions across the country. Meanwhile other health insurance companies have also initiative NWpG contract projects, and the number of enrolled patients has increased to about 9000.

For this purpose, the focus of this study is the analysis of effectiveness and cost-effectiveness of contracts for integrated care programmes according to NWpG compared to care as usual in real-world surroundings (routine-care) in five regions in Germany. The main outcome criteria are improvement of empowerment as well as improvement of patients’ subjective quality of life. Moreover, the effects of NWpG contracts for integrated care programmes on burden and quality of life of relatives will be evaluated. The results of this study will contribute to a better understanding of the need for outpatient and inpatient psychiatric care and will contribute to the development of current care concepts in Germany.

## Methods/design

### Study design

Although the randomised clinical trial is considered the gold standard for examining the efficacy of mental health care interventions, legal and organisational aspects prevent this design being applied in the current study: The implementation of integrated care programmes took place on the legal basis of the German social code which authorises the health insurances to define the criteria for the eligibility of patients to enrol in integrated care programmes. In addition, the social code gives patients the right to be informed by sickness funds about the opportunity to enrol in an integrated care programme. If a patient fulfils the eligibility criteria, he or she will be informed by the health insurance and asked for the permission to transmit his or her contact data to the local integrated care provider. After the patient gives his or her permission to the sickness fund the local service provider contacts the patient and invites him or her to attend an informative meeting. On the basis of this interview the service provider decides if the patient will be offered enrolment or not. Finally, the patient decides whether to enrol or not.

Therefore, we decided to design this study as a prospective observational controlled trial comparing patients with severe mental disorders enrolled in an NWpG integrated care programme with patients who received standard care in five federal states (Schleswig-Holstein, Northrhine-Westfalia, Berlin, Saxony and Bavaria) covering a broad range of catchment areas with different levels of urbanization, with different local mental health service systems and with different providers of ACT services. Trial duration is 18 months. Data will be collected at baseline and there will be three follow-ups after 6, 12 and 18 months.

Due to preference-based allocation blinding of patients is not feasible. Furthermore, it is not possible to blind the research associates because they would be unblinded at the latest documenting integrated care service use in the Client Socio-Demographic and Service Receipt Inventory (CSSRI).

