### Intervention

Participants in the intervention group receive access to integrated care services in addition to routine care. The agreements under the NWpG model for IC comprise the coordination and provision of outpatient psychiatric treatment and care services through mobile multi-professional teams under professional medical supervision.

Remuneration of IC contracts is based on staggered, case-related lump sums: On the one hand, it allows for extensive design flexibility in the programme by the service provider, on the other hand, it also transfers the risk of budget responsibility to the service provider. This risk results primarily from the fact that all costs for treatment in psychiatric inpatient and outpatient clinics must be financed from the lump sum. This so-called ‘malus’ regime does not apply to services by panel psychiatrists or psychotherapists [12].

All services will be documented in the Client Socio-Demographic and Service Receipt Inventory (CSSRI), and therefore, region-specific design options can be incorporated in the final analysis.

Integrated care according to NWpG contracts under § 140a et seq of Volume V of the Social Insurance Code shares the following basic components in each region:

• individual comprehensive case management on the basis of main control centres;

• outreach mental health services including social environment through home treatment;

• low-threshold and need adapted outreach therapeutic care by multi-professional teams under professional medical supervision, including psychiatric nursing, socio-therapy, psychotherapy, psycho-education and crisis intervention;

• guarantee for 24-hours crisis support 7 days a week;

• provision of retreat areas for crisis support outside hospital settings;

• continuous cooperation with patients, relatives and legal representatives to activate existing resources and to strengthen self-help potentials (empowerment) of those affected [12,13].

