### Trial recruitment process

A total of 500 patients, in detail 50 IC patients and 50 CAU patients in each of the five regions and half as many (250) relatives will be recruited via multiple settings. Recruitment will be organised by local research associates. The patients for the intervention group will be informed about the study mainly at introductory sessions for general registration for integrated care by service providers. Patient recruitment for the control group occurs with the assistance of cooperating psychiatric/psychosocial institutions (e.g. resident physicians and socio-psychiatric services). Moreover, patients who decline integrated care after the introductory session will be asked to participate in the control group. Posters and flyers advertising the study are also distributed at potential recruitment sites (e.g. medical practices).

Cooperating psychiatric health institutions that agreed to inform their patients about the study will exchange personal contact details of patients interested in the study with the associate on a regular basis. Written patient information is about the aim of the study, benefits and risks of participation and the study procedure. Subsequently, the associate contacts the patient and checks patient eligibility. If patients meet all of the inclusion and none of the exclusion criteria, they are selected for the study, and an appointment for visit 1 will be set. At visit 1, patients are asked to nominate a relative/informal carer who can be contacted by study staff regarding participation in the study. Patients should provide detailed information material about the study to the person nominated. If the person is interested, he or she is asked to contact the local research associate. If there is no reply, research associates will call the patient once again.

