### Ethical considerations

The informed consent procedure is described in the section “trial consent procedure”.

All patients enjoy freedom of choice as regards their utilisation of health-related services. However, routine care provision is expanded by integrated-care specific services (e.g. hometreatment) for patients registered in IC programmes. No patient group is disadvantaged regarding clinical care. Decisions concerning medical treatment and hospitalisation are performed by independent physicians as required. There are no adverse events expected to be related to the integrated care specific services.

Allocation to study groups depends on decisions of statutory health insurances and on patients’ preferences, completely independent of the study. No costs are imposed on patients, and all patients receive 10 € per visit to cover minor expenses.

The obtained data are strictly confidential.

Source documents are specified only by code. Using that code, data are entered into the electronic database. Source documents are maintained in a locked up cabinet in a room in the bureau of the local research associates or of the research coordinator settled at the University of Ulm. Source documents are scanned and sent by mail to the research coordinator for central data-entry just after the interview. Source documents are collected at study sites over two to three months, and will then be shipped to the research coordinator.

The research coordinator oversees the whole study procedure, and she receives progress reports of the project in each centre, if necessary, to make decisions with regard to recruitment strategies or undesired events.

The study is being conducted in compliance with the Declaration of Helsinki 2013.

It has been approved by the Ethics Committee of the University of Ulm on 3^rd^ May 2013 (application number: 129/13 and by the Ethics Committee of the TU Dresden on 30^th^ September 2013 (application number: EK 259072013).

This trial is registered with DRKS (German Clinical Trials Register) and ICTRP (International Clinical Trials Registry Platform) with the identifier DRKS00005111.

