## Discussion

This multi-centre controlled study examines the effectiveness and efficiency of contracts of integrated care in patients suffering serious mental illnesses in routine care surroundings. This is the first independent trial in Germany examining the impact of integrated care programmes pursuant to NWpG contracts on empowerment, quality of life, patient satisfaction and health economic measures.

As a major strength of this study, the effectiveness and the efficiency of integrated mental health care will be observed under real world conditions. Research in real life conditions might be more difficult but it will pay off further effort when it comes to external validity of the results. Since the intervention will be delivered by the local integrated care providers in the regional community mental health setting, it can be expected that service provision varies in spite of the fact that the same basic service components have to be provided in each region. In addition, study regions vary with regard to available standard care services and general living circumstances. Furthermore, the study sample will reflect the full heterogeneity of patients with severe mental illness. This heterogeneity of the real world setting provides the opportunity to examine the impact of a broad range of individual and environmental characteristics on the outcome of mental health care.

To make full use of this potential, high levels of academic rigour will be maintained by the involvement of independent, trained research associates and the application of standardised measurement tools, a strict monitoring and quality control for data collection and management and the application of advanced statistical methods for data analysis.

The preference-based allocation of study participants might be the major target of criticism as it is suspected to introduce a selection bias. Preference-based allocation was mainly chosen due to the legal and organisational framework of NWpG contracts in Germany. But it also holds the benefit of reality proximity of the intervention and thus contributes to external validity of study results. Selection bias will be controlled by means of propensity score adjustment. However, it cannot be guaranteed that all factors possibly causing a selection bias can be measured and included in the analysis.

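### The integrated care provider, who bears hospital costs, decides who is offered enrolment, and patients it refuses can still become controls: a risk of residual selection bias in the hospital-use and cost comparisons

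*Protocol article*

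**What the plan says.** The protocol article's Study design section describes three steps into IC. The insurer identifies and informs eligible patients. The local provider then holds an informative meeting: "On the basis of this interview the service provider decides if the patient will be offered enrolment or not". The patient decides last.

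The Intervention section describes the payment: "Remuneration of IC contracts is based on staggered, case-related lump sums". It says that budget risk passes to the provider, mainly because "all costs for treatment in psychiatric inpatient and outpatient clinics must be financed from the lump sum".

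Two later sections describe allocation without the provider's step. Ethical considerations: "Allocation to study groups depends on decisions of statutory health insurances and on patients’ preferences, completely independent of the study". Discussion: "The preference-based allocation of study participants might be the major target of criticism as it is suspected to introduce a selection bias".

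For controls, the Trial recruitment process section says: "Patient recruitment for the control group occurs with the assistance of cooperating psychiatric/psychosocial institutions". Posters and flyers are also used, and "patients who decline integrated care after the introductory session will be asked to participate in the control group". The inclusion and exclusion criteria contain nothing about a provider's decision. They assign the group by the type of care intended for the next 18 months.

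Hospital use, direct and indirect costs, and cost per QALY are secondary outcomes (Measurement instruments). Selection bias is to be handled by propensity scores built from broad classes of variables, among them medical history and clinical condition (Measures for bias control). The Discussion concedes that some selection factors may go unmeasured.

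**The concern.** The party that decides whether a patient is offered IC gains financially when its patients are rarely admitted, and admissions are among the study's outcomes. If the provider's decision reflects expected hospital use, IC patients will show fewer inpatient days and lower costs even when the programme has no effect.

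The route into the control group can add to this. A patient refused by the provider still meets every listed criterion, and the intended care is now standard care, so the allocation rule places that patient in CAU. Such a patient had no chance of receiving IC. That differs from a patient who declines an offer, and a propensity model cannot repair it merely by reweighting or adjusting among patients who could have gone either way.

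Because the sections that discuss allocation bias do not mention the provider's step, nothing in the plan is directed at it. The Conclusion section addresses the results to service providers and purchasers, for whom the cost comparison matters.

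**Working it through.** **1. Sections side by side.**

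| Topic | Section | Content |
|---|---|---|
| Who decides on the IC offer | Study design | Provider, after the insurer and before the patient |
| Provider's stake | Intervention | Hospital and clinic costs come from its lump sum |
| Account of allocation | Ethical considerations | Insurers and patient preference; provider not named |
| Account of bias | Discussion | Patient preference; provider not named |
| Control eligibility | Inclusion and exclusion criteria; recruitment process | No bar on provider-refused patients |
| Affected outcomes | Measurement instruments | Hospital use, costs, cost per QALY (secondary) |

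The later accounts are incomplete against the Study design section, and the control criteria leave the route for refused patients open.

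**2. Size before adjustment.** The protocol states no figure on this point, neither a refusal rate nor an admission rate, so there is nothing to reproduce. The inputs below are our assumptions:

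- 35% of patients admitted;
- correlation r between provider judgement J and latent risk Z of 0.2 or 0.4 (bivariate standard normal);
- the fraction q judged most at risk refused, with q = 5%, 10% or 20%;
- no treatment effect, and an unselected comparison group.

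A patient is admitted if Z > a = Φ⁻¹(0.65) and refused if J > b = Φ⁻¹(1 − q). If length of stay is unrelated to risk:

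reduction = 1 − [P(Z > a, J ≤ b) / (1 − q)] / 0.35.

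- r = 0.2, q = 5%: admission probability in those kept is 0.3415; 1 − 0.3415/0.35 = 2.4%.
- r = 0.4, q = 20%: 0.2941 in those kept; 1 − 0.2941/0.35 = 16.0%. Check: 0.8 × 0.2941 + 0.2 × 0.5734 (refused) = 0.350.

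If days among the admitted are proportional to exp(Z), so that the provider's judgement also predicts length of stay, the same ratio is taken with the indicator weighted by exp(Z).

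| r | q | Reduction, stay unrelated to risk | Reduction, stay rises with risk |
|---|---|---|---|
| 0.2 | 5% | 2.4% | 3.8% |
| 0.2 | 10% | 4.3% | 6.5% |
| 0.2 | 20% | 7.7% | 11.1% |
| 0.4 | 5% | 5.0% | 8.9% |
| 0.4 | 10% | 9.0% | 14.7% |
| 0.4 | 20% | 16.0% | 24.0% |

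Refused patients average 1.3 to 1.95 times the overall mean days in the first case and 1.4 to 2.7 times in the second. Each one who enters CAU widens the gap.

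**3. What adjustment would do.** This is a separate illustration, also on our assumptions: correlation 0.5 between provider impression and risk, 10%, 30% or 50% refused, controls unselected, no true effect. The unadjusted difference in risk is −0.5 × φ(b)/(1 − q) SD. For q = 10% this is −0.5 × 0.1755/0.9 = −0.10; for q = 50% it is −0.5 × 0.3989/0.5 = −0.40. Simulation of linear adjustment for a covariate explaining part of the risk gave:

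| Risk explained | 10% refused | 30% refused | 50% refused |
|---|---|---|---|
| 20% | −0.08 SD | −0.20 SD | −0.32 SD |
| 50% | −0.05 SD | −0.13 SD | −0.20 SD |
| 80% | −0.02 SD | −0.05 SD | −0.08 SD |

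Adjustment shrinks the difference, and good predictors of hospital use shrink it most. If providers do not select on risk, this step adds no bias.

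**The case against.** A reader might infer that the hospital-use and cost results are biased towards IC as a matter of fact. The documents do not support that. They say that the provider decides after an interview but give no criterion, so they show incentive and opportunity, not selection on admission risk. The lump sums are staggered and case-related. If payment rises with severity the incentive weakens, and the basis of the staggering is not stated. This stands, and it limits the point to a risk with a probable direction.

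A reader might also infer a flat contradiction about allocation. The ethics sentence does not claim to be exhaustive, its purpose is to say that the study does not influence allocation, and the Study design section discloses all three steps. Correcting the wording alone would be clerical.

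The protocol already plans propensity adjustment and admits that unmeasured selection may remain. Prior admissions fit naturally under medical history, and the exact covariates belong in the statistical analysis plan, which is not shown. This also stands: an unspecified covariate list is not an error here.

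The protocol names patients who decline, not patients who are refused, as a source of controls, and nothing shows how many refused patients exist. That is fair as to size, but the criteria still leave the route open.

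The upper illustrative range needs length of stay to rise with risk, and both ranges ignore adjustment. They show only what the mechanism could do.

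**Conclusion.** The point holds as a risk. A provider with a financial stake in hospital use takes a step in allocation that the later sections omit, and patients it refuses are not barred from the control group. The secondary hospital-use, cost and cost-utility comparisons are exposed to residual selection bias, probably towards IC.

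The size cannot be derived from the documents. Under the stated assumptions and before adjustment, IC inpatient days would be about 2.5% to 16% lower without any effect if length of stay is unrelated to risk, and about 4% to 24% lower if it rises with risk. The planned adjustment would reduce these figures. The point does not challenge the empowerment primary outcome or the sample size.

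**What to change.** 1. At the eligibility check, ask each potential control whether an IC provider has refused enrolment, and do not admit those who were refused. Flag any already enrolled and exclude them in a sensitivity analysis of the utilisation, cost and cost-utility outcomes.
2. Include admissions and inpatient days in the 12 months before entry in the propensity model for those outcomes. This can be written into the analysis plan; the eligibility criteria already ask about admission in that period.
3. Reconcile the Ethical considerations and Discussion sections with the Study design section by naming the provider's decision as a step in allocation.

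The cost is one screening question, one exclusion criterion and some wording. A few controls would be lost while CAU recruitment trails: at the reported status, 170 of 250 controls against 228 of 250 IC patients, so 80 and 22 remained to be recruited. With 398 of 500 already enrolled, much of the benefit would come from the flag and the sensitivity analysis.

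The remedy is partial. It relies on patients' reports of a refusal, and most controls never meet an IC provider, so those who would have been refused cannot be identified this way. For them, only adjustment for prior hospital use helps.
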